### 1.2. Aim and Hypothesis

This exploratory observational study primarily aims to assess whether differences in nutritional status and body composition—as indexed by bioimpedance-based assessment of body cell mass and hydration—exist between sedentary and physically active workers in the food supply chain.

As secondary exploratory aims, we will: (i) assess quality of life and emotional–affective well-being using validated instruments, in order to identify psychological or social critical issues related to work in the food supply chain; (ii) characterize nutritional status and dietary habits to detect potential deficiencies or excesses; (iii) quantify systemic biomarkers of oxidative stress and circulating serotonin levels; (iv) identify risk classes, i.e., subgroups of workers at potentially higher disease risk due to inadequate dietary patterns and/or exposure to occupational stressors; (v) assess sex-related differences in nutritional status, oxidative stress biomarkers, and psychological outcomes, to inform the potential need for gender-specific preventive or dietary recommendations; and (vi) analyze the standardized phase angle (SPhA) as an integrative marker of cellular health and systemic status, and explore its potential associations with nutritional, biochemical and psychological indicators on an exploratory basis.

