#### 3.2.2. Body Composition Assessment

Body composition assessment will be assessed using a tetrapolar bioelectrical impedance analysis (BIA) at a single frequency of 50 kHz (101 anniversary sports edition, Akern s.r.l., Florence, Italy). Bioelectrical impedance analysis (BIA) was performed using four certified electrodes (BIATRODES, Akern, Florence, Italy), arranged in two pairs positioned 5 cm apart on the metacarpal and metatarsal regions of the non-hemiparetic side. Measurements were taken with participants lying supine and with limbs positioned symmetrically. Prior to electrode placement, the skin was cleaned to ensure optimal conductivity and reduce potential artefacts. Individuals with fever or hypothermia were not assessed, as body temperature can influence electrical resistance. Hydration status was clinically evaluated before conducting BIA, and participants showing marked dehydration or peripheral edema were excluded. Subjects with implanted pacemakers were also not eligible. All operators received specific instructions to ensure correct data acquisition and minimize potential measurement errors.

Raw bioelectrical data consisted of Resistance (R, Ω) and Reactance (Xc, Ω) acquired under standardized conditions. These raw measures were exported and processed using the Bodygram^®^ analysis software (v. 3.3.19, Akern, Florence, Italy), which automatically computes derived impedance parameters according to the manufacturer’s validated algorithms (tissue hydration percentage, nutritional index, resistance, reactance, phase angle, standardized phase angle (SPhA), total body water, extracellular water, intracellular water, lean mass, fat mass, body cell mass, musculoskeletal mass, appendicular muscle mass, basal metabolic rate, and total daily energy expenditure).

Bioelectrical Impedance Vector Analysis (BIVA) will also be derived from raw data. Specifically, R and Xc were standardized by height (H, m) to obtain R/H and Xc/H, and the resulting values were plotted on the R–Xc plane to generate individual impedance vectors. The software provides BIVA graphical output as well as derived indices (e.g., vector length and phase angle), enabling subsequent group-level comparison of vector position. For an extensive description of BIVA, see Guerrini et al. [34].

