#### 3.3.2. Assessment of Biomarker of Systemic Oxidative Status

The systemic oxidative status will be analyzed through the following analyses on an integrated analytical photometer (Diacron International S.r.l., Grosseto, GR, Italy).

Total hydroperoxides colorimetric determination of ROMs (Reactive Oxygen Metabolites) (d-ROMs test; Diacron International S.r.l., Grosseto, GR, Italy). In the d-ROMs test, ROMs (primarily hydroperoxides) contained in the biological sample, close to iron, generate alkoxyl and peroxyl radicals, according to the Fenton’s reaction. The radicals, reacting with a chromogenic mixture, oxidize it and transform it into a photometrically measurable coloured derivative. The measurements are reported in arbitrary units (UCARR), where 1 UCARR corresponds to 0.08 mg/100 mL of hydrogen peroxide [40]. Values between 250 and 300 UCARR fall within the normal reference range; 301–320 UCARR are classified as borderline; 321–340 UCARR indicate low oxidative stress; 341–400 UCARR indicate moderate oxidative stress; 401–500 UCARR reflect high oxidative stress; and values exceeding 500 UCARR correspond to very high oxidative stress (Diacron International S.r.l., Grosseto, GR, Italy). The reproducibility of the test reported as CV% is 1.72.The total biological antioxidant capacity (BAP-Test; Diacron International S.r.l., Grosseto, GR, Italy) quantifies the overall pool of endogenous (e.g., bilirubin, uric acid, proteins) and exogenous (e.g., ascorbate, tocopherols, carotenoids, flavonoids) plasma components capable of exerting antioxidant activity and neutralizing reactive radical species. In the BAP test, the biological antioxidant potential of plasma barrier is based on the ability of all antioxidants active to reduce a coloured solution of ferric ions (Fe^3+^) to ferrous ions (Fe^2+^), resulting in a decolouration of the solution that is photometrically detectable. Reference values in µmol/L that are >2200 are intended as “normal antioxidant status”, 2200–2000 are considered a “border line antioxidant status, 2000–1800 are interpreted as “at slight antioxidant deficiency status”, 1800–1600 as “deficiency of antioxidant status”, <1600 as a “high and very high deficiency of antioxidant status” condition (Diacron International S.r.l., Grosseto, GR, Italy). The reproducibility of this test expressed as CV% is 2.32.Calculation of the OSI index to assess the relative antioxidant capacity, namely, the antioxidant capacity normalized for total circulating hydroperoxides. This index is the antioxidative/oxidative stress ratio assessed by the ratio equation: BAP/d-ROMs. We refer to this ratio as the OSI index, which reflects the system’s potential antioxidant capacity [44]. A threshold value of 7.3 was adopted for the BAP/d-ROMs ratio; values below this cut-off were classified as “oxidised,” whereas values equal to or above 7.3 were considered “reduced” [45].

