Standardized phase angle (SPhA), adjusted to sex- and age-specific references, will be analyzed as a continuous endpoint. The primary comparison (active vs. sedentary) will use a two-sample t-test. A sensitivity ANCOVA adjusting for BMI (and other prespecified covariates, if applicable) will assess robustness. The proportion of participants with SPhA ≤−1.65 (≈5th percentile) will be compared between groups using χ^2^ or Fisher’s exact test (reporting risk ratio and 95% CI). Secondary exploratory outcomes, deriving from nutritional, biochemical, and psychological domains’ assessment, will be analyzed with χ^2^/Fisher for categorical variables and t-test/Mann–Whitney for continuous variables depending on normality (assessed with Shapiro–Wilk). Effect sizes with 95% confidence intervals will be reported. Age will be included as a continuous covariate in sensitivity MAN(C)OVA and ANCOVA models. Exploratory analyses will also examine age-related associations with bioimpedance, psychological, and biomarker measures.

Exploratory associations among nutritional indicators (SPhA), bioimpedance parameters, oxidative-stress markers, serotonin, and psychological measures will be examined using Pearson or Spearman coefficients as appropriate. No directional hypotheses are pre-specified for these exploratory analyses; findings will be interpreted as hypothesis-generating.

No missing data are expected because all measurements will be collected during supervised in-person sessions. Data completeness will be verified at the time of assessment. If unexpected missingness occurs, analyses will follow a complete-case approach and the extent of missing data will be reported.

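### SPhA is to be correlated with bioimpedance parameters computed from the same resistance and reactance reading, so part of each such correlation is built in (minor)

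*Protocol article*

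**What the plan says.** Secondary aim (vi) in Section 1.2 is to "analyze the standardized phase angle (SPhA) as an integrative marker of cellular health and systemic status" and to explore its associations with nutritional, biochemical and psychological indicators.

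Section 3.6 gives the analysis: "Exploratory associations among nutritional indicators (SPhA), bioimpedance parameters, oxidative-stress markers, serotonin, and psychological measures will be examined using Pearson or Spearman coefficients as appropriate". It sets no directional hypotheses and calls the findings hypothesis-generating.

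Section 3.2.2 describes where the impedance variables come from. There is one tetrapolar measurement at a single frequency: "Raw bioelectrical data consisted of Resistance (R, Ω) and Reactance (Xc, Ω) acquired under standardized conditions". These go to the manufacturer's software, "which automatically computes derived impedance parameters according to the manufacturer’s validated algorithms". Its output list includes "resistance, reactance, phase angle, standardized phase angle (SPhA), total body water, extracellular water, intracellular water, lean mass, fat mass, body cell mass". For the vector analysis, "R and Xc were standardized by height (H, m) to obtain R/H and Xc/H".

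Section 3.2.2 stands under Section 3.2, Nutritional Status. Neither Section 3.2.2 nor Section 3.6 separates or flags pairs of variables that share the same raw reading.

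**The concern.** A correlation informs about two constructs only if the two variables could have been unrelated. Phase angle is the arctangent of Xc/R, and SPhA is that angle rescaled to sex- and age-specific references. The other bioimpedance parameters are functions of the same R and Xc, some combined with height or other inputs. SPhA will tend to correlate with several of them even where no health variable plays a part.

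What is at stake is how aim (vi) is read. Section 4 expects weak associations in the nutritional, biochemical and psychological domains, so coupled pairs could well be the largest entries in the table. Because Section 3.2 files body composition under nutritional status, a reader could take them as evidence that SPhA tracks nutrition. The hypothesis-generating label does not help, since a relation fixed by algebra generates no hypothesis.

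**Working it through.** The plan states no figure on this point, so there is none to reproduce. The check asks how large the correlations are when nothing but R, Xc and height enters the model.

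**Inputs**
- From the document: SPhA, phase angle, R/H and Xc/H all derive from one R and one Xc (Section 3.2.2). SPhA is adjusted to sex- and age-specific references, and N = 40 (Section 3.6).
- Assumed, not in the document: R 500 (SD 60) ohm, Xc 55 (SD 7) ohm, R–Xc correlation ρ from 0 to 0.8, height 1.70 (SD 0.07) m independent of both.

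**Step 1: SPhA against phase angle.** PhA = arctan(Xc/R) and SPhA = (PhA − reference mean)/reference SD. Within one sex and age stratum this is a linear rescaling, so r = 1.00. In a simulated sample of both sexes aged 18 to 65 (assumed mean R 470 and 570 ohm by sex, CVs 11% for R and 12% for Xc), r = 0.69 to 0.87.

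**Step 2: phase angle against R and Xc.** Let a = 60/500 = 0.120 and b = 7/55 = 0.127 be the coefficients of variation. For small angles PhA is nearly proportional to Xc/R, so approximately:

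- s = √(a² + b² − 2ρab)
- r(PhA, R) ≈ (ρb − a)/s
- r(PhA, Xc) ≈ (b − ρa)/s

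At ρ = 0, s = 0.175, giving −0.69 and +0.73. At ρ = 0.8, s = 0.0785, giving −0.23 and +0.40.

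**Step 3: divide by height.** The height CV is 0.07/1.70 = 0.041. Dividing by H shrinks the two correlations by about a/√(a² + 0.041²) = 0.95 and b/√(b² + 0.041²) = 0.95.

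Simulation of the exact arctangent gives:

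| ρ(R, Xc) | PhA–R | PhA–Xc | PhA–R/H | PhA–Xc/H |
|---|---|---|---|---|
| 0 | −0.69 | +0.71 | −0.65 | +0.67 |
| 0.3 | −0.56 | +0.61 | −0.53 | +0.58 |
| 0.5 | −0.46 | +0.53 | −0.44 | +0.50 |
| 0.7 | −0.33 | +0.44 | −0.31 | +0.42 |
| 0.8 | −0.24 | +0.39 | −0.22 | +0.37 |

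Within one stratum SPhA gives the same values as PhA. In the mixed-sex, mixed-age simulation of Step 1, SPhA gave −0.12 to −0.34 with R/H and +0.36 to +0.52 with Xc/H for ρ from 0.8 to 0.3. A simulated marker independent of R and Xc gave 0.00.

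**Step 4: sensitivity.** With CVs of 10% to 13% for R and 10% to 15% for Xc, and ρ from 0 to 0.8, the single-stratum range was −0.75 to +0.20 for R/H and −0.06 to +0.79 for Xc/H. Some combinations give almost no correlation.

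**Step 5: nominal significance at N = 40.** The critical |r| is 2.024/√(38 + 2.024²) = 0.312. By Fisher's z, with standard error 1/√37, a true |r| of 0.22 is significant in about 27% of studies, 0.33 in about 55%, 0.50 in about 92% and 0.70 in more than 99%.

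**Not computed.** Body cell mass, body water and lean mass share the inputs, but the manufacturer's algorithms are not given.

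**The case against.** The strongest reply is that little rests on these pairs. Section 3.6 is a one-sentence summary of domains, and the article says a full protocol and analysis plan exist, where individual pairs may be chosen or flagged. Aim (vi) names nutritional, biochemical and psychological indicators, not bioimpedance parameters, and nowhere says that an SPhA–bioimpedance correlation will count as evidence for the marker role. The analysis is exploratory throughout.

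Most of this stands as a limit on severity. It does not remove the point, because Section 3.6 itself names SPhA and bioimpedance parameters as classes to be associated, and Section 3.2 places body composition within nutritional status.

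Three stronger readings are tempting, and the document does not support them:

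- **That every coupled pair will be strong and surely significant.** This is near-certain only for phase angle. For R/H and Xc/H the size depends on the spread and correlation of R and Xc, and it can be near zero.
- **That the oxidative index has the same defect.** Section 3.3.2 defines it by a ratio ("This index is the antioxidative/oxidative stress ratio assessed by the ratio equation: BAP/d-ROMs"), so it would be coupled to its own components. But Section 3.6 does not announce a correlation of the index with BAP or d-ROMs.
- **That sure rejections would loosen the threshold for the other tests.** That needs a step-up procedure. Section 4 promises only some procedure to limit false positives, and under Bonferroni extra tests tighten the threshold instead.

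**Conclusion.** The point holds, at minor severity. Section 3.6 treats as distinct two classes of variable that Section 3.2.2 derives from one reading, so their correlations are partly or, for phase angle, almost wholly algebraic. Under R 500 (SD 60) and Xc 55 (SD 7) ohm with R–Xc correlation 0 to 0.8, the built-in part is about 0.2 to 0.7 in absolute size for R/H and Xc/H; other plausible spreads widen that range and include zero. For body cell mass and body water only the shared inputs can be shown, not the size.

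These pairs cannot support SPhA as an integrative marker. A reader might infer that aim (vi) as a whole is compromised, or that the primary result is. Neither follows. Correlations of SPhA with blood indices, oxidative-stress markers, serotonin and the questionnaires carry no such coupling. The primary Hotelling comparison, the sample size and the comparison of SPhA between groups are untouched.

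**What to change.** In Section 3.6, add a sentence that excludes pairs of SPhA or phase angle with any other variable derived from the impedance reading from the association tests, or that reports them in a separate table labelled as mathematically coupled. Either is sufficient.

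Rest aim (vi) on measures that do not come from that reading: blood indices, circumferences, the dietary survey, oxidative-stress markers, serotonin, BDI-II, BAI and SF-36. Apply whatever false-positive control is chosen to that set only. If the BAP/d-ROMs index is ever tabulated against BAP or d-ROMs, label that pair in the same way.

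The change needs no new data, participants or procedures. The only downside is that fewer correlations are reported as tests.

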### 3.6. Sample Size and Statistical Analysis

This is an exploratory, two-group study (active workers vs. sedentary workers). We planned a total sample of 40 participants (≈20 per group). A priori calculations were performed with G*Power (v3.1.9.7) to inform feasibility for a two-group multivariate comparison approximating Hotelling’s T^2^ (implemented as a MANOVA with two dependent variables, R/H and Xc/H). Under conventional assumptions (two-sided α = 0.05; target power ≈ 0.80; small-to-moderate multivariate effect), a sample size of 35 is typically adequate; therefore, we set N = 40 to accommodate measurement variability and potential attrition while maintaining balanced groups. Although the sample size calculation is fixed to the primary bioimpedance outcomes, the nutritional, biochemical, and psychological variables will be treated as exploratory secondary outcomes. For these, the study aims to estimate effect sizes and variability and to evaluate feasibility rather than to achieve confirmatory statistical power.

Raw R and Xc will be standardized by height (H) to obtain R/H and Xc/H. For each group, we will compute the mean vector and its 95% confidence ellipse on the RXc plane. The primary comparison between active vs. sedentary workers is the displacement of the mean impedance vector assessed with two-sample Hotelling’s T^2^ (reporting T^2^, *p*-value, Mahalanobis distance, and 95% CI for the mean-vector difference). Visualization will include the RXc-mean graph with group ellipses. Covariate-adjusted MAN(C)OVA models will be used as sensitivity analyses to assess robustness. In addition to age and sex—variables inherently related to BIVA interpretation—analyses will adjust for occupational factors (e.g., type of work tasks, years in role, ergonomic load) and lifestyle habits (e.g., smoking, alcohol consumption, physical activity outside work), which may influence hydration, body composition, metabolic state, or psychological indicators. Contemporary reference/tolerance ellipses for interpretation will follow Campa et al. [52] or the most appropriate sex-/age-specific set for our sample.

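### The exploratory correlations carry no adjustment for sex, so pairs of variables that are not sex-standardised and both differ by sex can appear associated

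*Protocol article*

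**What the plan says.** The association analysis is in section 3.6 of the protocol article. Its scope is "Exploratory associations among nutritional indicators (SPhA), bioimpedance parameters, oxidative-stress markers, serotonin, and psychological measures", and these "will be examined using Pearson or Spearman coefficients as appropriate". No partial, stratified or regression version is named. The results are labelled hypothesis-generating, with no directional hypotheses.

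Sex enters the plan in four other places:

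- **Group comparison (section 3.6).** "Covariate-adjusted MAN(C)OVA models will be used as sensitivity analyses to assess robustness". The text goes on: "In addition to age and sex—variables inherently related to BIVA interpretation—analyses will adjust for occupational factors". Both sentences stand in the paragraph on the active-versus-sedentary vector comparison.
- **SPhA (section 3.6).** "Standardized phase angle (SPhA), adjusted to sex- and age-specific references, will be analyzed as a continuous endpoint".
- **Impedance vector (section 3.6).** "Raw R and Xc will be standardized by height (H) to obtain R/H and Xc/H". Height is the only scaling described.
- **Aim (v) (section 1.2).** The study will "assess sex-related differences in nutritional status, oxidative stress biomarkers, and psychological outcomes".

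The adjusted models mentioned in section 2.2 concern chronic conditions and medications; sex is not in that list.

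**The concern.** A correlation computed over two sexes mixes the relation within each sex with the relation between the two sex means. If both variables have different means in men and women, the pooled coefficient is non-zero even when the variables are unrelated within each sex.

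The protocol gives reason to think that sex matters on both sides of many pairs. It calls age and sex "variables inherently related to BIVA interpretation", and it makes sex differences in nutritional, oxidative-stress and psychological outcomes a study aim. The coefficient it then names has no place for sex. Adjusting the Hotelling's T² comparison or the SPhA t-test does not help, because those are different analyses.

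At stake is how the hypothesis-generating output is read. Some links between domains could be sex differences under another name, and section 4 intends multidomain patterns to inform later prevention work.

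**Working it through.** The article gives no figure for the correlation analysis, so there is none to reproduce.

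**Inputs**

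- N = 40, from section 3.6.
- Two-sided α = 0.05. Section 3.6 states it for the primary comparison; it is assumed here for the correlations.
- p, the share of one sex: not given. 50% is the base case, with 30% and 20% as alternatives.
- d1 and d2, the sex differences of the two variables in within-sex SD units: not given. Assumed from 0 to 1.5.
- Correlation within each sex: zero, so every significant result is a false positive.

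**Step 1: correlation induced by sex alone**

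r = p(1−p)·d1·d2 / √[(1 + p(1−p)·d1²)(1 + p(1−p)·d2²)]

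At p = 0.5, p(1−p) = 0.25:

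- d1 = d2 = 0.5: 0.0625 / 1.0625 = 0.06
- d1 = d2 = 0.8: 0.16 / 1.16 = 0.14
- d1 = d2 = 1: 0.25 / 1.25 = 0.20
- d1 = 1.5, d2 = 0.8: 0.30 / √(1.5625 × 1.16) = 0.22
- d1 = d2 = 1.5: 0.5625 / 1.5625 = 0.36
- d1 = 0 with any d2: 0

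**Step 2: false-positive rate at N = 40**

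The rates come from 20,000 simulated studies per row (40,000 for the row with 1 and 1), using Pearson coefficients and normal data, with equal numbers of each sex.

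| d1, d2 (assumed) | induced r | pooled coefficient | sex-adjusted partial |
|---|---|---|---|
| 0, 1.5 | 0.00 | 5.1% | 4.8% |
| 0.3, 0.3 | 0.02 | 4.7% | 4.6% |
| 0.5, 0.5 | 0.06 | 6.9% | 5.2% |
| 0.8, 0.8 | 0.14 | 13.8% | 4.8% |
| 1, 1 | 0.20 | 24% | about 5% |
| 1.5, 0.8 | 0.22 | 28.9% | 4.8% |
| 1.5, 1.5 | 0.36 | 67.4% | 5.0% |

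A hand check uses Fisher's z with standard error 1/√37. For r = 0.20, atanh(0.20) × √37 = 0.203 × 6.083 = 1.23. The chance of exceeding 1.96 is then P(Z > 0.73), about 23%, in line with the simulated 24%.

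**Step 3: unequal sex split**

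- With 30% of one sex, the pooled rates are 11.7% (0.8, 0.8), 19% (1, 1), 23% (1.5, 0.8) and 56% (1.5, 1.5).
- With 20% of one sex, they are 9.0% (0.8, 0.8), 16.7% (1.5, 0.8) and 39.7% (1.5, 1.5).

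The sex-adjusted partial coefficient stays at about 5% in all of these.

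**Step 4: price of adjusting**

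The smallest significant |r| is t/√(df + t²). Pooled, df = 38: 2.024/√(38 + 2.024²) = 0.312. Partial for sex, df = 37: 2.026/√(37 + 2.026²) = 0.316. Separate analyses at 20 per sex would need 0.444.

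**The case against.** Four points can be made for the plan.

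1. **SPhA is already standardised.** Aim (vi) concerns SPhA, and SPhA is adjusted to sex- and age-specific references. The first row of the table shows that with no sex difference in one variable the pooled test holds its 5%. This stands. A reader might infer that the output of aim (vi) would consist largely of sex differences, or that the plan controls for sex nowhere in its associations. The documents support neither.

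2. **Pooling is not stated.** The article names the type of coefficient only, the full protocol and analysis plan are not shown, and a partial coefficient is still a Pearson or Spearman coefficient. It is also true that the adjustment sentence in section 3.6 mentions psychological and metabolic factors, which are not outcomes of the R/H–Xc/H model, so it could be read more widely. This stands in part. The sentence directly follows the MAN(C)OVA sensitivity models, and an unqualified coefficient is plainly read as pooled, but that remains a reading.

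3. **The sizes are assumed.** The article reports no sex difference and no sex split, and aim (v) proposes to assess differences without predicting them. This stands. A reader might infer that any two variables will appear associated, or might take differences of 2 SD and conclude that false positives are near certain. Both variables must differ by sex, differences of 0.3–0.5 SD do little harm, and nothing in the documents supports 2 SD.

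4. **The results are only exploratory.** They are labelled hypothesis-generating, and section 4 promises procedures to limit false positives if multiple exploratory tests are run. This does not answer the point. Such procedures deal with chance findings, whereas the sex-induced correlation is systematic.

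**Conclusion.** The point holds for a limited set of pairs: those in which neither variable is sex-standardised and both differ by sex. R/H or Xc/H with a biomarker or a psychological score is the clearest candidate; two such markers or scores with each other are another. For these pairs the method as written can return an association that sex alone produces.

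At N = 40 with equal numbers of men and women, the false-positive rate depends on the assumed sex differences. It runs from close to nominal when they are small, through about one in four at 1 SD in both variables, to about two in three at 1.5 SD in both. An unequal sex split lowers these rates. The figures also assume normal data, no correlation within sex and Pearson coefficients; Spearman coefficients were not simulated. The protection of SPhA pairs depends on how well the reference values fit this sample.

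The primary comparison is not affected. This is an inexpensive improvement to an exploratory analysis and is worth making before the associations are computed.

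**What to change.** In section 3.6, state that for pairs not involving SPhA the main association analysis is the partial Pearson or Spearman correlation adjusted for sex and for age as a continuous covariate. Give the unadjusted coefficients as a supplement and mark the points by sex in the plots. If the full analysis plan already specifies this, one sentence in the article saying so is enough.

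The change is one of wording. Sex and age are already covered by the planned data collection, and the adjustment costs one degree of freedom for sex and one for age. Partial correlation is preferable to separate analyses by sex, which would raise the detectable correlation far more.
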